### Statistical Analysis and Sample Size Calculation

First, the patient population will be randomly split in two groups: the first group will consist of 80% of the sample population and will be used for developing the model, while the second group (20% of the sample population) will be used to estimate the performance of the model developed. For the development of a new prediction model, we will apply least absolute shrinkage and selection operator (LASSO) as a tool for efficient variable selection to develop the multivariable logistic regression model. For this, we will use the glmnet library (Version 3.0-2). To find the regulation parameter λ, 20-fold cross-validation is applied. To gain some robustness in the choice for the optimal model, we will use the λ.1se option. As quantification of the model fit, the area under the curve (AUC) from the 20% testing portion of the sample population will be presented.

Previous studies on time to circulatory death in cDCD patients found that approximately 50% to 70% will die within 60 minutes after WLST [3,7,15,23,25]. We estimated that approximately 50% of our cohort will have circulatory death within this time frame, which is balanced to patients that will die after this time frame. The sample size determination for our study was based on including enough patients to reach a sufficient level of precision for the AUC for the 20% testing group. Our goal is to have a 95% confidence interval for the AUC with a width of 0.16. This translates into a standard error of 0.04 for the AUC. With an expected AUC of approximately 0.84 and a population with balanced outcomes (50% mortality within 60 minutes of WLST), this requires a sample of N=100. As we will split our patient population into an 80% development portion and a 20% portion for assessing predictive performance, this study requires the inclusion of 400 patients overall.

Second, previously published prediction models will be externally validated using our data set of 400 patients [7,15,25]. We will use logistic regression models with death within 60 minutes (yes/no) as the outcome. These models will be applied to the validation data and performance of the models will be assessed in terms of discrimination and calibration. The calibration process will consist of three steps. First, a calibration plot will be made for the original predictor. Second, the coefficients of the original predictor will be shrunk by multiplying them by the slope of the calibration curve. For this shrunken predictor, a new calibration curve is fitted. Third, calibration will be completed by adjusting the original intercept with the intercept from the calibration curve with the shrunken coefficients. The models will be refitted in the new data set.

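### The new model's AUC rests on one random holdout of 80 patients; resampling the whole procedure on all 400 would roughly halve its error

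*Protocol article*

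**What the plan says.** All of this stands in the Protocol article, Methods, Statistical Analysis and Sample Size Calculation.

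- Design: "the patient population will be randomly split in two groups".
- Development: "the first group will consist of 80% of the sample population and will be used for developing the model".
- Evaluation: "the second group (20% of the sample population) will be used to estimate the performance of the model developed", and "the area under the curve (AUC) from the 20% testing portion of the sample population will be presented".
- Cross-validation serves only to choose the penalty: "To find the regulation parameter λ, 20-fold cross-validation is applied".
- Precision: "Our goal is to have a 95% confidence interval for the AUC with a width of 0.16", and "This translates into a standard error of 0.04 for the AUC". The section takes an expected AUC of 0.84 and 50% events, derives a test group of 100, and gives a total of 400.

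For the new model the article describes neither a resampled performance estimate nor a refit on all patients. The previously published models, by contrast, are to be validated on the full 400.

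**The concern.** Developing the model is the primary objective, and its reported performance comes from one random fifth of the cohort. The 320 development patients add nothing to that estimate, and a different random draw would give a different AUC. Because the split is random within one cohort from the same six hospitals, it is internal validation only. It offers no test in a new period or place that would offset the lost precision.

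The Introduction describes existing tools as too inaccurate for practice. An AUC known only to about ±0.09 is a weak basis for saying that the new model does better. The older models would also be assessed on five times as many patients as the new one.

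**Working it through.** **Inputs from the article:** AUC 0.84; 50% events (earlier studies: 50% to 70%); test group of 100; total 400; split 80/20; target SE 0.04 and CI width 0.16.

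**Formula (Hanley-McNeil).** With A the AUC, P1 = A/(2−A) and P2 = 2A²/(1+A):

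SE² = [A(1−A) + (n1−1)(P1−A²) + (n0−1)(P2−A²)] / (n1·n0)

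At A = 0.84: P1 = 0.7241, P2 = 0.7670, A² = 0.7056 and A(1−A) = 0.1344. The two differences sum to 0.0185 + 0.0614 = 0.0799.

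**Step 1: the plan's own figure.** For 50/50: SE² = (0.1344 + 49 × 0.0799)/2500 = 0.00162, so SE = 0.0402 and width = 2 × 1.96 × 0.0402 = 0.158. The test group of 100 reproduces. The total does not: 100/0.20 = 500, and 20% of 400 is 80.

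**Step 2: the holdout as planned.** For 40/40: SE² = (0.1344 + 39 × 0.0799)/1600 = 0.00203, so SE = 0.0451 and width = 0.177. At 60% or 70% events the width is 0.171. Two other variance formulas give 0.172 (equal-variance binormal) and 0.199 (Obuchowski).

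**Step 3: all 400, by formula.** For 200/200: SE = 0.0200 and width = 0.078, a ratio to Step 2 of 0.44. This is a best case, because it treats the model as fixed and tested on 400 independent patients. Resampling also carries the noise of refitting.

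**Step 4: simulation with the whole LASSO procedure repeated.** Each cohort had 400 patients. RMSE is taken around the true AUC of the model being assessed. Implied width is 3.92 × RMSE.

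| Setting (assumed) | Split RMSE | Resampling RMSE | Ratio | Implied width, split | Implied width, resampling |
|---|---|---|---|---|---|
| 30 candidates, 8 real, 156 runs | 0.0435 | 0.0205 (10-fold CV) | 0.47 | 0.171 | 0.080 |
| 30 candidates, 8 real, 200 runs | 0.0442 | 0.0228 (CV), 0.0224 (bootstrap) | 0.52, 0.51 | 0.173 | 0.089, 0.088 |
| 60 candidates, 8 real, 150 runs | 0.0478 | 0.0258 (CV), 0.0256 (bootstrap) | 0.54, 0.54 | 0.187 | 0.101, 0.100 |

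The last two rows used normal predictors with correlation 0.2, a squared-error lasso in place of the logistic one, 10-fold choice of λ, CV repeated twice, and only 15 bootstrap samples per run. In those rows the split's mean bias was +0.001 and −0.002.

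**Step 5: the model itself.** True AUC when built on 320 against 400 patients: 0.835 against 0.841, 0.814 against 0.818, and 0.827 against 0.832. The gain is about 0.005.

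**Step 6: how much is the luck of the split.** For a fixed score, drawing 80 from one given cohort of 400 has SD of about 0.0451 × √(1 − 80/400) = 0.040. A direct check gave 0.039. Around 0.84 that is 0.84 ± 1.96 × 0.040, or about 0.76 to 0.92.

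**The case against.** A holdout is a valid method. The article states it openly, builds the sample size on it and accepts a stated precision. That stands: the holdout AUC is not biased for the model it tests, so the complaint is about efficiency.

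A locked test set also protects against choices that a bootstrap cannot replay, such as variable coding, which of the three measurement time points to use, and which CT features to enter. That stands too. A reader might infer that the split buys nothing, and this is the reason not to say so.

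Other stronger readings also fail:

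- *The missed 0.16 target proves that splitting is wrong.* It does not. With 100 test patients the split meets the target (width 0.158). The miss comes from the separate slip between 100 and 20% of 400.
- *A fifth of the data is lost to the model, which is materially worse for it.* The simulated loss is about 0.005 in AUC, small beside either method's error.
- *The published coefficients will ignore a fifth of the cohort.* The article does not say which fit will be published, and a condensed article may leave a final refit to the full plan.
- *Resampling gives a width of 0.078.* That is the fixed-model figure from Step 3. The simulations support about 0.08 to 0.10.
- *Unequal event counts in the test group do harm.* A random 80 would hold 32 to 48 events (95% range), but stratifying by outcome moved the SD only from 0.0392 to 0.0390.

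**Conclusion.** The point holds as one of inefficiency. The single holdout gives an AUC with SE of about 0.045 and CI width of about 0.177, and the result depends on one arbitrary draw. Resampling the whole procedure on all 400 would have roughly half the error (RMSE 0.020 to 0.026 against 0.043 to 0.048). Its implied width of about 0.08 to 0.10 meets the 0.16 goal without more patients.

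The formula ratio of 0.44 is stable for AUC 0.75 to 0.90 and for 50% to 70% events. The simulated ratios of 0.47 to 0.54 rest on predictor numbers and correlations that the documents do not give. All figures assume that the target of 400 was reached. The planned analysis is not invalid, but a clearly more precise one is available from the same data.

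**What to change.** Replace the split with wording such as: *The model will be developed on all patients. Every modelling step, including the choice of λ, will be repeated in at least 500 bootstrap samples, or in repeated 10-fold cross-validation, to give an optimism-corrected AUC and calibration.* State how the confidence interval is formed, since the plain formula at n = 400 ignores refitting and is somewhat too narrow.

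Rewrite the sample size paragraph to give precision for all 400. This also removes the conflict between a test group of 100 and 20% of 400, which under the present split would need 500 patients although the Abstract reports enrolment as complete.

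The change needs new wording and computing time: 500 bootstrap samples with 20-fold choice of λ mean 500 × 21 = 10,500 LASSO path fits. It needs no new data. The real loss is the locked test set, so coding, time-point and CT-feature choices should be fixed in writing before the outcome is analysed.

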Necessary steps to be taken before the initiation of a cDCD procedure are as follows: prognostication, making the decision to withdraw life-sustaining treatment, and approaching family and obtaining their consent for organ donation. Initiation of end-of-life care in acute settings and inexperience in organ donation practices outside ICUs have a negative impact on the number of potential donors [19,20]. Postponing the discontinuation of medical treatment gives professionals more time to guide families adequately and inform them about the dying process and organ donation [21]. Data collected about end-of-life decision-making can provide more insight into whether a patient may be eligible for a cDCD procedure based on time to circulatory death. Such insight can be useful when giving grieving families estimations of time to death and the likelihood that a donation procedure could be performed. However, studies on this important topic are lacking.

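### The new prediction model is to be judged by AUC, with calibration planned only for the published models, so the stated plan cannot show whether its predicted risks are right

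*Protocol article*

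**What the plan says.** All of the following is in the protocol article, Statistical Analysis and Sample Size Calculation, unless stated otherwise.

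- **New model, method.** LASSO is used "as a tool for efficient variable selection to develop the multivariable logistic regression model". On the penalty: "To find the regulation parameter λ, 20-fold cross-validation is applied", and "To gain some robustness in the choice for the optimal model, we will use the λ.1se option". The text does not say whether the penalised coefficients, or an unpenalised refit of the selected variables, form the final model.
- **New model, performance.** The 80/20 random split reserves 20% of patients for assessing performance. The one measure named is the AUC: "As quantification of the model fit, the area under the curve (AUC) from the 20% testing portion of the sample population will be presented".
- **Published models.** For these, "performance of the models will be assessed in terms of discrimination and calibration". Three steps follow: a calibration plot, shrinkage of the coefficients by the calibration slope, and correction of the intercept.
- **Use.** The Discussion expects the model to help staff guide families, to improve prediction of the chance of donation, and to help manage team resources. The Background speaks of "giving grieving families estimations of time to death and the likelihood that a donation procedure could be performed".
- **Reporting.** The Results section commits to STROBE and TRIPOD without listing performance measures.

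**The concern.** The article calls AUC a quantification of model fit, and it is not one. Any increasing transformation of the predicted risks leaves AUC unchanged. A model that says 80% where the truth is 93%, or the reverse, can have the same AUC as a correct one.

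The text also treats the two sets of models unequally. It sets out calibration in three steps for the comparators and names only a ranking measure for the model that is the primary objective. Telling a family or a transplant team how likely donation is requires a correct probability as well as a correct ranking. Both ways of finishing a LASSO model at λ.1se can be expected to distort that probability: the first by shrinkage, the second by overfitting after selection.

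**Working it through.** **Inputs from the article.** Total 400; split 80/20, so 0.80 × 400 = 320 for development and 0.20 × 400 = 80 for testing; 20-fold cross-validation; λ.1se; expected AUC 0.84; 50% of patients dying within 60 minutes.

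**The plan's own precision figure.** Hanley-McNeil variance with A = 0.84 and n per outcome group:

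SE² = [A(1−A) + (n−1)(q1−A²) + (n−1)(q2−A²)] / n², where q1 = A/(2−A) = 0.724 and q2 = 2A²/(1+A) = 0.767.

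- n = 50 (100 patients): SE = 0.0402 and width 2 × 1.96 × 0.0402 = 0.158. This reproduces the stated 0.04 and 0.16.
- n = 40 (80 patients, which is 20% of 400): SE = 0.045 and width 0.177.

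The mismatch between 100 and 80 is a separate matter. What counts here is that the planned precision concerns AUC only.

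**Why AUC is blind.** If the linear predictor L is replaced by a + bL with b > 0, the order of patients is unchanged. AUC is then exactly unchanged, whatever a and b are. Calibration intercept and slope are this a and b.

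**Simulation.** The article text gives neither the number of candidate predictors nor their effects, so these are assumptions: 15, 30 or 60 candidates, 6 or 10 true predictors, pairwise correlation 0.2, true AUC 0.86 or 0.80. R glmnet 4.1-10 was used (the plan names 3.0-2), with 20-fold cross-validation on deviance, n = 320, 60 runs per scenario and evaluation in 20,000 new patients. Means:

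| Candidates / true predictors / true AUC | Slope, λ.1se kept | Slope, λ.min | Slope, refit after λ.1se | AUC, λ.1se | AUC, λ.min | Top decile, predicted / observed (λ.1se) | Bottom decile, predicted / observed (λ.1se) |
|---|---|---|---|---|---|---|---|
| 15 / 6 / 0.86 | 1.571 | 1.080 | 0.902 | 0.844 | 0.851 | 0.870 / 0.947 | 0.124 / 0.050 |
| 30 / 6 / 0.86 | 1.579 | 1.128 | 0.834 | 0.839 | 0.845 | 0.868 / 0.955 | 0.133 / 0.049 |
| 60 / 10 / 0.86 | 1.465 | 1.057 | 0.708 | 0.818 | 0.827 | 0.863 / 0.933 | 0.145 / 0.071 |
| 30 / 6 / 0.80 | 1.566 | 1.080 | 0.796 | 0.771 | 0.779 | 0.791 / 0.898 | 0.210 / 0.123 |

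With the penalised coefficients kept, the slope exceeded 1 in every run. Mean predicted minus observed risk lay between −0.002 and 0.004.

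**Cross-checks with other assumptions and code.**

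- With 20 or 40 candidates and true AUC 0.84, one simulation gave penalised slopes of 1.68 and 1.75.
- Another with 20 or 40 candidates gave 1.64 to 1.68 penalised and 0.83 to 0.86 refitted, with AUC between 0.81 and 0.83 throughout.
- A separate implementation with 15, 30 and 60 candidates (25 runs each) gave AUC, penalised against refitted, of 0.837 v 0.843, 0.834 v 0.837 and 0.823 v 0.826. These differences of 0.003 to 0.006 are small beside the AUC standard error of 0.045 in 80 patients, yet the mean slopes fell on opposite sides of 1.

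**What a slope means for a stated risk.**

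- *Penalised, slope 1.579, intercept near 0.* Predicted 0.868 has logit 1.883; 1.579 × 1.883 = 2.974, a risk of 0.951 (simulated 0.955). Predicted 0.133 has logit −1.875; 1.579 × (−1.875) = −2.960, a risk of 0.049 (simulated 0.049).
- *Refit, intercept taken as 0.* Predicted 0.95 has logit 2.944. Slope 0.834 gives a risk of 0.921, and slope 0.708 gives 0.889.

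**What 80 test patients can show.** For the penalised model the slope had a standard error of about 0.36 to 0.40. A slope of 1.5 with standard error 0.40 has a 95% interval of 1.5 ± 1.96 × 0.40, or 0.72 to 2.28. The interval lay wholly above 1 in only 8% to 32% of runs. With 100 test patients the standard error would be about √(80/100) = 0.894 times as large, so 0.32 to 0.36.

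**The case against.** **The direction is not fixed by the text.** A reader might infer that λ.1se is bound to over-shrink the risks. The article calls LASSO a variable-selection tool, which allows an unpenalised refit, and the refit errs the other way. This stands: the direction is conditional. It does not remove the point, because mean slopes departed from 1 under both readings and AUC separated neither.

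**Calibration may be planned elsewhere.** A reader might infer that no planned analysis will detect the problem. The documents do not support that. The article is condensed, a fuller plan may exist, it does not say that AUC is the only measure, and it commits to TRIPOD. What can be said is that none is stated here for the new model. The point still holds on the written text, which spells out calibration for one set of models and labels AUC as model fit for the other.

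**The comparison with published models.** A reader might infer that comparing an uncalibrated new model with recalibrated older ones is unfair. For AUC it is not, since recalibration with a positive slope leaves AUC unchanged. Only a comparison of calibration would be lacking.

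**λ.1se is a declared choice, made for robustness.** This stands. Changing to λ.min, or adding predictive values at risk cut-offs, is a preference and not a correction.

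**The Background sentence on families** concerns insight from data on end-of-life decisions rather than the new model. This is largely fair; the Discussion carries the argument on intended use.

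**Conclusion.** The point holds in limited form. As written, the plan measures the ranking ability of its primary model and calls this fit. It reserves calibration for the secondary comparators, although the intended use needs correct probabilities.

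Under the assumed predictor sets, the calibration slope would be about 1.5 to 1.7 if the λ.1se coefficients are kept and about 0.7 to 0.9 if the selected variables are refitted, with almost the same AUC. In the glmnet runs, keeping the penalised coefficients put the extreme deciles off by roughly 7 to 11 percentage points: at the top, 0.933 − 0.863 = 0.070 to 0.898 − 0.791 = 0.107; at the bottom, 0.124 − 0.050 = 0.074 to 0.210 − 0.123 = 0.087. Average risk was about right, so the predictions are not wrong throughout.

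These sizes depend on assumed numbers, effects and correlations of predictors, and the real ones may differ. The conclusion that AUC cannot show miscalibration depends on no such assumption. This is a worthwhile correction to the analysis of the primary objective. It does not invalidate the study.

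**What to change.** 1. State whether the final model uses the LASSO coefficients at λ.1se or an unpenalised refit of the selected variables.
2. For the new model, report a calibration plot, calibration slope and calibration intercept alongside the AUC, and describe the AUC as discrimination, not as model fit.
3. Estimate slope and intercept by cross-validation or bootstrap in the development data, repeating the whole procedure, including the choice of λ and the selection of variables, in each resample. Use these estimates to correct the coefficients and then the intercept, in the way the article already sets out for the published models.
4. Report calibration in the 20% test portion with confidence intervals as a secondary check, and say that it is imprecise at that size.

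λ.1se can stay. The cost is a modest amount of extra analysis on existing data (the Abstract gives data collection as completed in April 2020), and possibly a less favourable account of the model's performance.

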**Methods:**

In this multicenter observational prospective cohort study, all patients admitted to the intensive care unit of 3 university hospitals and 3 teaching hospitals who met the criteria of the cDCD protocol as defined by the Dutch Transplant Foundation were included. The target of enrolment was set to 400 patients. Previously developed models will be refitted in our data set. To further update previous prediction models, we will apply least absolute shrinkage and selection operator (LASSO) as a tool for efficient variable selection to develop the multivariable logistic regression model.

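### The total of 400 does not follow from the sample size calculation: a 20% test portion of 400 is 80 patients, not the 100 that the stated AUC precision needs

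*Protocol article*

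**What the plan says.** The section Statistical Analysis and Sample Size Calculation opens with a random split: 80% of patients to develop the LASSO logistic model and 20% to estimate its performance. The AUC in that 20% is the measure of fit to be reported.

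The sample size is derived from the same 20%. The stated basis is "including enough patients to reach a sufficient level of precision for the AUC for the 20% testing group". The target is explicit: "Our goal is to have a 95% confidence interval for the AUC with a width of 0.16", followed by "This translates into a standard error of 0.04 for the AUC". With an expected AUC of about 0.84 and balanced outcomes, the article says "this requires a sample of N=100". It then refers again to the 80/20 split and concludes that "this study requires the inclusion of 400 patients overall".

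The Methods part of the Abstract repeats the total: "The target of enrolment was set to 400 patients". The paragraph on external validation also works with 400 patients. Nowhere does the article give a different split, another reason for 400, or an allowance for losses.

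**The concern.** The 100 patients are tied to the test portion, and the test portion is 20% of the total. A total of 400 makes that portion 80. So the total, the split and the required test size cannot all be true together.

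The precision of the test-set AUC is the only justification given for the sample size, and that AUC is the performance measure for the primary objective, the new prediction model. The article commits to TRIPOD reporting, so the justification is likely to be carried into the results paper. Readers would then be told of a precision that the design does not provide.

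**Working it through.** **Inputs, all from Statistical Analysis and Sample Size Calculation**

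- Target: 95% interval of full width 0.16, standard error (SE) 0.04. Check: 0.16 / (2 × 1.96) = 0.0408, which rounds to 0.04.
- Expected AUC: A = 0.84.
- Outcome: 50% dying within 60 minutes, so equal groups.
- Required test sample: 100. Split: 80/20. Total: 400.

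The article does not name its formula. I used Hanley-McNeil:

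SE² = [A(1−A) + (n₁−1)(Q₁−A²) + (n₀−1)(Q₂−A²)] / (n₁n₀), with Q₁ = A/(2−A) and Q₂ = 2A²/(1+A).

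At A = 0.84:

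- A² = 0.7056 and A(1−A) = 0.1344
- Q₁ = 0.84/1.16 = 0.7241, so Q₁−A² = 0.0185
- Q₂ = 1.4112/1.84 = 0.7670, so Q₂−A² = 0.0614
- The two differences sum to 0.0799 (from unrounded values).

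**Step 1: the article's 100.** With 50/50, SE² = (0.1344 + 49 × 0.0799)/2500 = 0.00162. SE = 0.0402 and width = 3.92 × 0.0402 = 0.158. Solving for the sample gives 102 patients for SE 0.04 and 98 for SE 0.0408. The figure of 100 is reproduced.

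**Step 2: the article's 400.** 100/0.20 = 500, and 0.20 × 400 = 80. The figure of 400 is not reproduced. A total of 400 yields 100 test patients only with a 25% share (100/0.25 = 400). Reading 100 as the development set does not help either: 100/0.80 = 125.

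**Step 3: precision with 80 test patients.** With 40/40, SE² = (0.1344 + 39 × 0.0799)/1600 = 0.00203. SE = 0.0451 and width = 0.177. Scaling the article's own target, with no AUC formula at all, gives 0.16 × √(100/80) = 0.179.

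**Step 4: does the choice of formula matter?** At AUC 0.84 with balanced outcomes:

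| Method | Width, n = 80 | Width, n = 100 | Test patients for SE 0.04 to 0.0408 | Total at 20% |
|---|---|---|---|---|
| Hanley-McNeil | 0.177 | 0.158 | 102 to 98 | 510 to 490 |
| Equal-variance binormal | 0.172 | 0.153 | 96 to 92 | 480 to 460 |
| Obuchowski approximation | 0.199 | 0.178 | 129 to 124 | 645 to 620 |

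No method gives a total of 400; the smallest is 460. None gives a width of 0.16 with 80 patients.

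**Step 5: do nearby inputs rescue it?** The article cites 50% to 70% deaths within 60 minutes. With 80 patients and AUC 0.84, the Hanley-McNeil width is 0.171 at both 60% and 70%, and the binormal width is 0.175 and 0.187. By Hanley-McNeil with balanced outcomes, 80 patients give a width of 0.166 at AUC 0.86 and 0.154 at AUC 0.88. The target would therefore be met only if the AUC were clearly above the planned value.

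**The case against.** The best defence is that little is lost. The interval grows by less than 0.01 on each side. The target is a precision goal built on an approximate AUC, and no hypothesis test or power depends on it. The AUC estimate is not biased. External validation of the published models uses the whole cohort and is untouched.

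All of that stands, and it limits how serious the consequence is. It does not repair the calculation. The article sets out every input and then draws a total that they do not support. The sentences are intact in the text, and the step is not one left to a separate analysis plan, because it is carried out in full here.

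A second fair point concerns the remedy: changing the split now, after data collection has ended, would itself be a change to the plan and has to be reported as one. That stands too, and it is a reason to prefer restating the precision.

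**Conclusion.** The sample size justification is wrong as written. The requirement of 100 test patients is sound; the conversion to a total of 400 is not. At the stated split the test portion is 20 patients short, or equivalently the study is 100 patients short. The expected SE is 0.045 instead of 0.04, and the width is 0.177 instead of 0.16. That is about 10% wider than the stated target (0.1767/0.16 = 1.10), or 12% wider than the same formula gives for 100 patients (0.1767/0.1578 = 1.12).

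The arithmetic contradiction rests on no assumption. The size of the loss assumes AUC 0.84, balanced outcomes, Hanley-McNeil variance and exactly 400 usable patients. The binormal and Obuchowski methods put the width at 0.172 and 0.199. Patients without usable data would widen it further.

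**What to change.** Enrolment closed in July 2018 and data collection in April 2020, so the correction has to work with the patients in hand.

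- **Preferred: keep 80/20 and correct the paragraph.** Suggested wording: the 20% test portion of 400 patients will hold 80 patients; at an expected AUC of 0.84 with balanced outcomes this gives a standard error of about 0.045 and a 95% confidence interval of width about 0.18. This costs only wording and a slightly less favourable stated precision. If the number of usable patients is not 400, compute from the actual number.
- **Alternative: a 75/25 split, 300 for development and 100 for testing.** This gives SE 0.040 and width 0.158, so the target is met. It moves 20 patients from development to test. It should be fixed and documented as a change before the data are split or any model is fitted. If that has already happened, use the first option.

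Whichever is chosen, state the test-set size explicitly, and carry the corrected justification into the results paper.
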